### 3.9 Statistical analysis

The primary outcome is nutritional recovery. Secondary outcomes include hospitalization, average daily weight gain among recovered children, defaulting, and relapse within 3 months.

All analyses will use the intention-to-treat principle and account for the stratified cluster design. We will use generalized estimating equations and robust standard errors to compare the proportion of children recovered, hospitalized, defaulted or relapsed within 3 months, and mixed effects models to compare average daily weight gain.

Interim analysis at 6 months of inclusion will be conducted to ensure the safety of children included. No adjustment will be made for multiple testing. All P values will be 2-sided, with  $P < 0.05$  considered statistically significant. Analyses will be performed using SAS version 9.3 or higher (SAS Institute Inc., Cary, NC).

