## 2.0 STUDY OBJECTIVES AND ENDPOINTS

The study aims to strengthen the evidence base for more flexible ways to deliver nutritional treatment in humanitarian crises.

Primary objective:

To estimate the effectiveness of monthly vs. standard weekly follow up in the treatment of uncomplicated severe acute malnutrition in children aged 6 to 59 months in terms of nutritional recovery.

Secondary objectives:

- To estimate the effectiveness of monthly vs. standard weekly follow up in the treatment of uncomplicated severe acute malnutrition in children aged 6 to 59 months in terms of hospitalization.
- To estimate the effectiveness of monthly vs. standard weekly follow up in the treatment of uncomplicated severe acute malnutrition in children aged 6 to 59 months in terms of weight gain among recovered children.
- To estimate the effect of monthly vs. standard weekly follow up in the treatment of uncomplicated severe acute malnutrition in children aged 6 to 59 months in terms of the risk of defaulting.
- To estimate the effectiveness of monthly vs. standard weekly follow up in the treatment of uncomplicated severe acute malnutrition in children aged 6 to 59 months in terms of the risk of relapse within 3 months following discharge.
- To estimate program coverage in areas receiving monthly vs. standard weekly follow up in the treatment of uncomplicated severe acute malnutrition in children aged 6 to 59.
- To assess the cost-effectiveness of monthly vs. standard weekly follow up in the treatment of uncomplicated severe acute malnutrition in children aged 6 to 59 months in terms of cost per child treated and per child recovered.

Primary endpoint:

The primary endpoint is nutritional recovery, defined by being free from medical complications, MUAC  $\geq$  125 mm, and no edema for 2 weeks if admitted with edema.

Secondary endpoints:

- Hospitalization, defined as referral to inpatient care for :

- weight/edema changes: weight loss over 3 weeks; static weight over 4 weeks; onset of edema when previously absent; persistent edema 3 weeks following admission
  - failed appetite test
  - clinical complication necessitating inpatient care: fever, hypothermia, severe dehydration, repeated vomiting, severe respiratory distress, chest in-drawing, severe pallor with respiratory distress, malaria with signs of severity, abscess or extended skin lesions, very weak, apathy or unconscious, or convulsions

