### 3.7 Power calculations

Ten outpatient therapeutic feeding centers in this setting can be expected to admit total of 3,500 children for the treatment of uncomplicated SAM over 12 months (3,777 children admitted at 10 facilities in 2016). Assuming a baseline risk of nutritional recovery in the weekly

follow-up group of 0.80, intraclass correlation of 0.002 and significance level of 0.05 using the one-sided Score test, and allowing for 20% loss to follow up, a sample size of 350 children per health facility (2100 per group) will achieve 88% power to detect a non-inferiority margin difference between the group proportions of -0.05.

|                        | Difference in recovery between weekly vs. monthly follow up groups (n = 350 per site) |                  |                  |
|------------------------|---------------------------------------------------------------------------------------|------------------|------------------|
| Intraclass correlation | $\Delta = -0.15$                                                                      | $\Delta = -0.10$ | $\Delta = -0.05$ |
| 0.001                  | 1.00                                                                                  | 1.00             | 0.94             |
| 0.002                  | 1.00                                                                                  | 1.00             | 0.88             |
| 0.01                   | 1.00                                                                                  | 0.97             | 0.54             |

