### 4.3 Evaluation of eligibility

Evaluation of eligibility will occur at the time of first visit/admission to the study outpatient therapeutic feeding centers. Upon arrival, program staff will screen children for eligibility for outpatient treatment as per standard protocol (e.g. age 6 to 59 months; MUAC < 115 mm or grade 1-2 edema; and absence of illness requiring inpatient management). Anthropometry (weight to the nearest 100 g; length (children <24 months) or stature (children ≥ 24 months) to the nearest 0.1 cm; and MUAC to the nearest 0.1 cm using the UNICEF band) will be assessed by program staff using standard techniques described for the WHO Multicenter Growth Reference Study. All study and program staff will be trained and standardized prior to beginning data collection. Standardization sessions will be repeated every 3 months during data collection. Children ineligible for outpatient treatment will not be admitted for nutritional therapy and asked to return home, with explanation of the program admission criteria. These children may be referred to the primary pediatric care program or vaccination program, as needed.

If the child is eligible for outpatient treatment, a study nurse will evaluate the specific study inclusion and exclusion criterion (e.g. new admission, no peanut allergy). If a child presenting to a site assigned to weekly follow-up is eligible for SAM treatment but found ineligible for study inclusion, the child will receive all medical and nutritional treatment with standard weekly follow up at the same site without participating in study data collections. If a child presenting to a site assigned to monthly follow-up is eligible for SAM treatment but does not participate in the study (e.g. parent declines to provide consent or child does not meet inclusion criteria), the child will receive all medical and nutritional treatment with standard weekly follow up at the same site without participating in study data collections. Non-participating children seeking care at sites assigned to monthly follow-up will receive standard care, while all other eligible and participating children included at the monthly site will continue to receive the alternative monthly follow-up as per the random assignment of the site.

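### Section 3.9 names no baseline covariate for the primary recovery comparison; pre-naming admission MUAC, edema and age would be a cheap safeguard with 10 openly recruiting centers

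*Protocol*

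**What the plan says.** Protocol section 3.9 gives the primary method: "We will use generalized estimating equations and robust standard errors to compare the proportion of children recovered, hospitalized, defaulted or relapsed within 3 months". It adds that analyses follow intention to treat and take account of the stratified cluster design. It names no baseline covariate and excludes none.

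Section 2.0 states: "The primary endpoint is nutritional recovery, defined by being free from medical complications, MUAC" of at least 125 mm, with two edema-free weeks for children admitted with edema. Section 3.4 admits children aged 6 to 59 months with MUAC below 115 mm, grade 1-2 edema, or both. At eligibility screening (section 4.3), "MUAC to the nearest 0.1 cm using the UNICEF band) will be assessed by program staff using standard techniques". Age, MUAC and edema are therefore established for every child before consent.

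Section 3.6 stratifies the randomization of the 10 centers by number of admissions and by nothing else, and describes the study as open. Under sections 4.3 and 5.3, a child at a monthly site whose caregiver declines consent receives weekly follow-up.

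**The concern.** Recovery is a threshold on a variable measured at entry. For most children, admission MUAC is the starting distance from that threshold, and edema at admission adds a further condition. Follow-up ends at 12 weeks, so children who start further away plausibly recover less often within the window.

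Arms could differ in starting severity in two ways. The first is chance: with five centers per arm, enrolling many children per center does not average out differences between centers, and stratifying by size helps only as far as size tracks severity. The second is recruitment. Caregivers are approached when the center's arm is already fixed and known. At a weekly site, declining leaves the schedule unchanged; at a monthly site, declining brings weekly visits. Section 3.4 also lets staff exclude a child judged a poor candidate for retention, subject to validation by the Field Investigator. If caregivers of sicker children more often decline monthly visits, the monthly arm enrolls milder cases and non-inferiority becomes easier to show. Intention to treat among enrolled children does not correct this.

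At stake are the credibility of a conclusion against a 5-point margin and some precision. There is also freedom to choose covariates after an imbalance has been seen, unless they are named beforehand.

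**Working it through.** **Inputs from protocol section 3.7.** Recovery and ICC: "follow-up group of 0.80, intraclass correlation of 0.002". Test: one-sided score test at 0.05. Result: "will achieve 88% power to detect a non-inferiority margin difference between the group proportions of -0.05". Size: 350 children per center, five centers per arm. Equal true recovery of 0.80 in both arms is taken for the calculation.

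**Inputs not in the protocol (assumed).** Share of outcome variance explained by admission MUAC, edema and age: within centers (R2w) 0 to 0.20, between centers (R2b) 0 to 0.50. ICC of a baseline severity score: 0.01 to 0.05. Correlation of that score with recovery: 0.2 to 0.4.

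**Step 1: reproduce the 88%.** With k = 5 and m = 350,

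SE = sqrt(2 × 0.80 × 0.20 × (1 + 349 × 0.002) / (5 × 350)) = sqrt(0.32 × 1.698 / 1750) = 0.0176.

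Power = Φ(0.05/0.0176 − 1.645) = 0.884 (0.883 with the restricted null variance of the score test). The other entries at a difference of -0.05 also reproduce: 0.938 at ICC 0.001 (printed 0.94) and 0.538 at ICC 0.01 (printed 0.54). The match needs 350 analyzed children per center; with 280 (20% loss) power is 0.842. The printed 2100 per group is a separate matter.

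**Step 2: precision after adjustment.**

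SE² = 2p(1 − p) × [(1 − ICC)(1 − R2w)/(mk) + ICC(1 − R2b)/k].

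| Setting (one-sided 0.05) | Unadjusted | R2w 0.05 | R2w 0.10 | R2w 0.20 |
|---|---|---|---|---|
| m = 350, ICC 0.002, R2b = 0 | 0.884 | 0.892 | 0.900 | 0.916 |
| m = 280, ICC 0.002, R2b = 0 | 0.842 | 0.853 | 0.863 | 0.884 |
| m = 350, ICC 0.01, R2b = 0 | 0.540 | 0.544 | 0.548 | 0.556 |

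If only within-center variance is explained, the gain is about 1 to 3 points at 350 per center, 1 to 4 at 280, and under 2 at ICC 0.01. If between-center variance is explained too (R2w 0.10 with R2b 0.20 or 0.50, m = 350), power is 0.922 or 0.952 at ICC 0.002, and 0.610 or 0.736 at ICC 0.01.

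**Step 3: chance imbalance.** The SD of the arm difference in a standardized severity score, with m = 280, is sqrt((2/5) × (ICCx + (1 − ICCx)/280)). This is 0.074, 0.097 and 0.146 for ICCx of 0.01, 0.02 and 0.05. The outcome SD is sqrt(0.80 × 0.20) = 0.40, so a 1-SD imbalance shifts the recovery difference by 0.40 × correlation × that SD:

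- smallest: 0.40 × 0.2 × 0.074 = 0.6 points;
- middle: 0.40 × 0.3 × 0.097 = 1.2 points;
- largest: 0.40 × 0.4 × 0.146 = 2.3 points.

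These inputs should also be compatible with the outcome ICC. If the score acts equally within and between centers, it contributes correlation² × ICCx to that ICC. The largest case gives 0.16 × 0.05 = 0.008, which fits the protocol's 0.01 row but not its 0.002. Grid combinations that stay within 0.002 (such as 0.09 × 0.02 = 0.0018) give shifts of up to about 1.2 points.

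**Step 4: selective enrolment.** The protocol gives nothing from which to size this. As a conversion only, each 0.1 SD difference in mean severity between arms moves the recovery difference by 0.40 × (0.2 to 0.4) × 0.1 = 0.8 to 1.6 points.

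**The case against.** The strongest objection is that section 3.9 is silent on adjustment. GEE accepts covariates, and a covariate list is normally left to the SAP, which was not available here. A reader might infer that the protocol chose a crude comparison and deliberately omitted severity; the text does not support that. Nor does it support saying that protection against imbalance is lost: randomization is stratified by size and the analysis accounts for it, so protection is incomplete. A design-adjusted comparison is a valid analysis.

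Second, chance differences in severity between centers are already part of the outcome ICC and so of the unadjusted standard error (1.76 points at ICC 0.002). That stands: for chance imbalance, adjustment improves precision and does not remove an unrecognized bias. It does not answer selective enrolment, which is a systematic shift that the standard error does not cover.

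Third, a reader might expect a large power gain by assuming a correlation of 0.5 with recovery. That would mean 0.5 × 0.40 = 20 points of recovery per SD of severity, and nothing in the protocol supports it. Children admitted on edema can enter at any MUAC, and non-recovery may also reflect default, which admission MUAC need not predict.

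Finally, with 10 clusters a robust variance is delicate, and added covariates do not help it. This stands as a condition on how the adjustment is carried out.

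**Conclusion.** The point holds as a recommendation to improve the primary analysis. It does not correct an error: no stated figure is wrong. What stands is that the method named for the primary endpoint accounts for design only, in an open 10-center trial where starting severity is closely tied to the definition of recovery and enrolment follows a known allocation.

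The precision benefit is modest on the within-center assumption, and larger figures depend on between-center variance explained, for which the protocol offers no input. The imbalance range likewise rests on assumed score ICCs and correlations, and its upper part goes with an outcome ICC near 0.01. Adjustment deals only with the measured part of any selective enrolment. It also relies on admission measurements being comparable across arms, since they are taken by staff who know the center's assignment.

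**What to change.** In section 3.9, state that the primary recovery comparison adjusts for admission MUAC (continuous), edema at admission (yes/no), age and the center-size stratum. Report the result as a standardized difference in proportions, so that it stays on the scale of the -0.05 margin. Use cluster-level inference suited to 10 centers: either standardization from the GEE with a small-sample correction, or a two-stage analysis of covariate-adjusted center residuals. Show the unadjusted difference as supportive.

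The cost is one or two sentences and a little more programming, with no new data collection. If an SAP already specifies this, a cross-reference in section 3.9 is enough.

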### 3.0 METHODOLOGY

#### 3.1 Study design

This study will be conducted as a stratified cluster randomized trial of a monthly schedule of follow up in the treatment of uncomplicated SAM among children aged 6 to 59 months. The unit of randomization will be the outpatient therapeutic feeding center. The 10 health centers supported by UNICEF will be stratified by size ( $\pm 500$  admissions per site), and centers within a stratum will be randomized in a 1:1 ratio to one of two schedules of treatment: (1) standard weekly visits or (2) monthly visits with support for home-based surveillance.

Distribution of the therapeutic feeding rations, as well as medical and anthropometric surveillance, will take place on a weekly or monthly basis until discharge according to the random assignment of the site. Caregivers in the monthly visit group will receive additional instruction at admission regarding home-based MUAC measurement and clinical surveillance.

Regardless of intervention assignment, all children with uncomplicated SAM will receive standard medical care on admission as per national guidelines, and a home visit 3 months following discharge from the nutritional program. Additional data collection, including coverage assessment and economic costing analysis will be used to address the secondary objectives related to the evaluation of coverage and cost-effectiveness, respectively.

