#### 3.3. Study sites

Study activities will take place in 10 outpatient therapeutic feeding centers supported by UNICEF. The 10 outpatient therapeutic feeding centers will be staffed by research nurses trained to seek written informed consent and support data collection during all enrollment and follow-up visits. Children transferred for inpatient care will be followed by a research nurse until hospital discharge. Once medical complications are resolved, appetite has returned and/or edema is reduced, the child will resume treatment at the original outpatient therapeutic feeding center and study follow-up until program discharge.

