### 3.6 Random allocation and concealment

The reduced schedule of follow-up will be tested using a stratified cluster randomized design, with the health center as the unit of randomization. All children admitted for outpatient therapeutic feeding at a participating health center will receive the same schedule of follow-up.

Health centers will be stratified by size according to the number of admissions per site in order to promote balance of the intervention among children. Centers within a stratum will be randomized in 1:1 ratio to standard weekly vs. monthly follow-up. Randomization assignment will be made by lottery, in which a local representative will select the name of one of the two interventions from an envelope or opaque jar.

The study will be open, as it will not be possible to blind participants or study staff to frequency of follow up received.

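### GEE with ordinary robust standard errors on only 10 centers understates the standard error and roughly doubles the type I error of the primary test

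*Protocol*

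**What the plan says.** Section 3.1 fixes the independent unit: "The unit of randomization will be the outpatient therapeutic feeding center". Section 3.3 fixes how many there are: "Study activities will take place in 10 outpatient therapeutic feeding centers supported by UNICEF". Section 3.6 gives the allocation: "Centers within a stratum will be randomized in 1:1 ratio to standard weekly vs. monthly follow-up". That leaves about 5 centers per arm.

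Section 3.9 names the analysis of the binary outcomes: "We will use generalized estimating equations and robust standard errors to compare the proportion of children recovered, hospitalized, defaulted or relapsed within 3 months". It adds: "All analyses will use the intention-to-treat principle and account for the stratified cluster design". This implies at least one stratum parameter besides the arm effect. For testing it says "All P values will be 2-sided, with" a threshold of 0.05.

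No section mentions a small-sample variance correction, a t or F reference, degrees of freedom, a permutation test or a center-level analysis. The power calculation in section 3.7 makes no such allowance either. Its inputs are a baseline recovery in the weekly "follow-up group of 0.80, intraclass correlation of 0.002 and significance level of 0.05 using the one-sided Score test".

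**The concern.** The sandwich variance is estimated from the between-center scatter of residual totals, so its quality depends on the number of centers and not on the number of children. With 10 centers two errors add up. The estimate is biased downward because the fitted parameters absorb part of the scatter. It is also noisy, and a normal reference treats it as known.

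The aim is to show that monthly visits recover nearly as many children as weekly visits, within a margin of 5 percentage points. Limits that are too narrow make a false non-inferiority claim more likely than the stated error rate. Hospitalization, defaulting and relapse are to be analyzed in the same way, so their intervals are affected too.

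**Working it through.** **Inputs.** J = 10 centers, 5 per arm (sections 3.1, 3.3, 3.6). Recovery 0.80, ICC 0.002, one-sided 0.05, margin -0.05, 350 children per site (section 3.7). Two-sided 0.05 (section 3.9). q = 2 parameters with arm only, or 3 with one stratum term. The number of strata parameters is an assumption drawn from the single size split in section 3.1.

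**1. The plan's own power.** A Farrington-Manning score test with true difference 0, design effect 1 + (350 - 1) × ICC, a normal reference and 350 analyzed at each of 5 sites per arm gives 0.938, 0.883 and 0.538 for ICC 0.001, 0.002 and 0.01. The protocol's table shows 0.94, 0.88 and 0.54. The table is reproduced, and only with a normal reference.

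**2. Bias of the standard error.** For equal centers the uncorrected sandwich variance averages (J - q)/J of the true variance.
- Arm only: √(8/10) = 0.894, so about 11% too small.
- Arm and stratum: √(7/10) = 0.837, so about 16% too small.

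**3. Actual size of the Wald z test.** Size = P(t on J - q df > z × √((J - q)/J)), doubled for a two-sided test.

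| Nominal level | Arm only (8 df) | Arm and stratum (7 df) |
|---|---|---|
| one-sided 5%, z = 1.645 | 9.0% | 10.6% |
| two-sided 5%, z = 1.96 | 11.8% | 14.5% |
| one-sided 2.5%, z = 1.96 | 5.9% | 7.3% |

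**4. Width of correct 95% limits relative to the planned ones.** Arm only: 2.306/(1.96 × 0.894) = 1.32. With stratum: 2.365/(1.96 × 0.837) = 1.44.

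**5. Simulation.** Beta-binomial data, 20,000 trials per setting, ICC 0 to 0.05:
- Equal sites, two-sided 5%: 11.5-11.8% with arm only, 14.2-15.0% with stratum.
- Unequal sites (assumed 144 to 549 analyzed per site, strata split 6/4): 12.9-17.7%.
- One-sided 5% with the true difference at the -0.05 margin: 9.1% with arm only, 10.5% with stratum.
- A logit-link exchangeable GEE at ICC 0.002, 300 runs, two-sided 5%: 12.3% and 14.0%.

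With equal sites the inflation barely changes with the ICC, so a small ICC gives no protection.

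**6. After correction.** A Kauermann-Carroll variance with a t reference on 8 or 7 df gives two-sided size 4.6-5.2% with equal sites and 5.4-6.5% with unequal sites.

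**7. Power with the t reference.** ICC 0.002. SE = √(2 × 0.16/(5m) × (1 + (m - 1) × 0.002)), which is 0.01762 for m = 350 and 0.01887 for m = 280 (350 less 20% loss). Power is from the noncentral t with noncentrality 0.05/SE.

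| Analyzed per site | Level | Normal | 8 df | 7 df |
|---|---|---|---|---|
| 350 | one-sided 0.05 | 88% | 83% | 82% |
| 350 | two-sided 0.05 | 81% | 70% | 68% |
| 280 | one-sided 0.05 | 84% | 78% | 77% |
| 280 | two-sided 0.05 | 75% | 64% | 63% |

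**The case against.** The strongest objection is that the protocol never says uncorrected or normal reference. A bias-corrected sandwich is still a robust standard error and would fit the present wording, and a statistical analysis plan that is not shown could specify it. This is possible. But the unqualified phrase ordinarily means the uncorrected estimator, nothing in the protocol excludes that form, and following the text in its usual sense gives a wrong error rate. The issue is therefore a named method that fails with 10 clusters, and not only a missing detail.

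Second, the doubling belongs to the Wald z test. A robust GEE score test is much closer to nominal. With equal centers and arm only, its size is about 5.6% at two-sided 5% and 6.2% at one-sided 5%. With a stratum term, simulation gave 7.0-7.6% two-sided and 6.7-8.2% one-sided. This stands as a limit on the claim. However, the score test is named only for the power calculation, and a non-inferiority claim needs a confidence limit, which section 3.9 pairs with robust standard errors.

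Third, section 3.7 uses one-sided 0.05 and section 3.9 two-sided 0.05, so the nominal rate is itself ambiguous. If non-inferiority is read from a two-sided 95% limit, the false-claim rate is 5.9-7.3%. That is 1.2 to 1.5 times 5%, but 2.4 to 2.9 times the 2.5% such a limit should deliver. The inflation is present on either reading.

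Last, the protocol gives no site sizes, so the unequal-site figures rest on assumed sizes. The equal-site results do not need them.

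**Conclusion.** The concern holds. Read in its ordinary sense, the planned analysis understates the standard error by about 11% (arm only) to 16% (with a stratum term). It raises the type I error to 1.8-2.1 times nominal for the one-sided 5% test and 2.4-2.9 times for the two-sided 5% test. Unequal site sizes would make it somewhat worse.

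These figures assume a Wald test or interval with the uncorrected sandwich variance, a normal reference, 10 centers and at most one stratum parameter. Because this governs the validity of the primary conclusion, it must be fixed before analysis.

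**What to change.** In section 3.9, replace the unqualified reference to robust standard errors with one of the following:

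- GEE with a bias-corrected sandwich variance (Kauermann-Carroll or Fay-Graubard) and a t reference on clusters minus cluster-level parameters, which is 7 with arm and one stratum term; or
- a stratified t analysis of center-level recovery proportions.

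Apply the same rule to hospitalization, defaulting and relapse, and use small-sample degrees of freedom (Kenward-Roger) in the weight-gain mixed model. The corrected analysis is available in SAS (PROC GLIMMIX), the software already named. A Mancl-DeRouen variance with a t reference also controls the error, but it was conservative here (2.5-4.0% at nominal two-sided 5%).

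State in the same edit which level and sidedness govern the non-inferiority decision, since sections 3.7 and 3.9 differ.

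No change to conduct or data collection is needed. The cost is wider intervals and lower stated power. At 7 df and ICC 0.002, one-sided 0.05 gives 82% with 350 analyzed per site and 77% with 280. At two-sided 0.05 the figures are 68% and 63%. Section 3.7 should be restated to match. Its sample-size sentence also needs checking: it reads "allowing for 20% loss to follow up, a sample size of 350 children per health facility (2100 per group", yet 350 at 5 sites is 1,750 per group, and the 88% is reproduced only if all 1,750 are analyzed.

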## 1.3 Innovation and relevance for the community-based management of SAM

The outpatient management of SAM has been recommended by the World Health Organization, WFP, UN Standing Committee on Nutrition and UNICEF since 2007. However, reliance on a weekly schedule of follow up limits operations to areas where access and frequent visits to a health facility are possible and potentially reduces the number of children receiving treatment. In contexts where weekly follow up is not feasible (e.g. Chad where access was limited due to heavy rains; Somalia where access is reduced due to high insecurity), programs have been forced to curtail operations, resulting in fewer children receiving treatment. Similarly in contexts where the absolute number of children needing treatment is very high (e.g. northeastern Nigeria), the burden of the traditional schedule of follow up can limit coverage and reduce program impact. To our knowledge, no program has implemented a reduced schedule of follow up (beyond biweekly visits) and documented safety or efficacy. This proposal therefore represents innovation as this is the first time a strategic reduction in the schedule of follow up will be implemented and evaluated within the community-based treatment model.

This study is intended to provide programs with greater flexibility to consider more innovative models of treatment and to extend operations into areas previously unsuitable for treatment programs. If the results of this study can confirm that monthly visits in the treatment of uncomplicated SAM can achieve similar rates of nutritional recovery as standard weekly visits, programs will have the evidence needed to consider adopting a reduced schedule of follow up and provide treatment in a greater number of settings. Evidence provided by this study could support increased coverage in existing programs, as a reduced schedule of follow up in an existing program could decrease the program burden per child and allow for an increase in the proportion of children covered using the same or fewer resources. These results could also allow more flexible and innovative programming in new settings where the standard protocol has been impractical, including contexts with nomadic populations, difficult geographical access, conflict or high incidence of malnutrition.

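### Section 3.7 sizes a one-sided 0.05 non-inferiority test against -0.05, but Section 3.9 makes every P value 2-sided at 0.05 and gives no margin rule for the primary outcome

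*Protocol*

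**What the plan says.** Protocol Section 3.7 bases the sample size on a "significance level of 0.05 using the one-sided Score test", with weekly "follow-up group of 0.80, intraclass correlation of 0.002", and concludes that the trial "will achieve 88% power to detect a non-inferiority margin difference between the group proportions of -0.05". This is a non-inferiority design with a fixed margin.

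Protocol Section 3.9 names nutritional recovery as the primary outcome and plans to compare proportions by generalized estimating equations (GEE) with robust standard errors. It then sets a blanket rule: "All P values will be 2-sided", significant below 0.05. It does not exempt the primary outcome, mention non-inferiority, repeat the margin or say which confidence limit decides.

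Elsewhere, Section 2.0 words the primary objective as estimation only. Section 1.3 gives the hoped-for conclusion, that monthly visits "can achieve similar rates of nutritional recovery as standard weekly visits". The margin and the one-sided test appear only in the power section.

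**The concern.** A one-sided test against -0.05 and a 2-sided test of zero difference answer different questions and can give different answers on the same data. With no margin attached, a 2-sided P value tests zero difference by default. Failure to reject zero is not evidence that monthly follow-up is at most 5 points worse.

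The alpha conflicts as well. If the 2-sided 0.05 level is kept and its 95% confidence limit is compared with the margin, the non-inferiority test runs at one-sided 0.025, and the power in Section 3.7 no longer applies.

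At stake is the primary conclusion of an open trial meant to support a move from weekly to monthly visits. As the text stands, both the hypothesis and the error level could be settled after results are known.

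**Working it through.** **Inputs.** From Section 3.7: weekly recovery 0.80, margin -0.05, one-sided alpha 0.05, ICC 0.001, 0.002 or 0.01, 350 children per site, 20% loss. From Section 3.1: 10 centers randomized 1:1, taken as 5 per arm. Assumption: the power is computed at a true difference of 0. The protocol does not say so, but this value reproduces its table.

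**Step 1: reproduce the stated power.** With m children analysed per site:

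- n_eff = 5m / (1 + (m - 1) x ICC)
- SE = sqrt(2 x 0.80 x 0.20 / n_eff)
- power = Phi(0.05/SE - z)

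For m = 350 and ICC 0.002, n_eff = 1750/1.698 = 1030.6 and SE = sqrt(0.32/1030.6) = 0.0176. Power at one-sided 0.05 = Phi(2.838 - 1.645) = 88.4%. The restricted variance of the Farrington-Manning score test gives 88.3%. The protocol states 88%. At ICC 0.001 and 0.01 the results are 93.8% and 54.0%, against 0.94 and 0.54 stated. The table is therefore a one-sided 0.05 non-inferiority calculation with 350 analysed per site.

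**Step 2: the same calculation at one-sided 0.025** (95% confidence limit against -0.05, z = 1.96).

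| ICC | One-sided 0.05, m = 350 | One-sided 0.025, m = 350 | One-sided 0.025, m = 280 |
|---|---|---|---|
| 0.001 | 93.8% | 88.9% | 83.3% |
| 0.002 | 88.4% | 81.0% | 75.5% |
| 0.01 | 54.0% | 41.5% | 39.7% |

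The last column takes the 20% loss out of 350 (350 x 0.8 = 280). At ICC 0.002 this gives n_eff = 1400/1.558 = 898.6 and SE = 0.0189. The restricted variance gives 75.3%.

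**Step 3: where the two sections disagree** (ICC 0.002, m = 350, SE 0.0176).

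- The 2-sided 0.05 test of zero difference is non-significant, on the unfavorable side, for estimates above -1.96 x 0.0176 = -0.035.
- Non-inferiority at one-sided 0.05 needs an estimate above -0.05 + 1.645 x 0.0176 = -0.021.
- An estimate between about -0.035 and -0.021 shows no significant difference and yet fails non-inferiority.

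**Step 4: error rate if P >= 0.05 were read as similar.** Let true recovery be 0.80 weekly and 0.75 monthly. Then SE = sqrt((0.16 + 0.1875)/n_eff), and the chance of a non-significant result is about 1 - Phi(0.05/SE - 1.96).

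- ICC 0.002, m = 350: SE = 0.0184, chance about 22%.
- ICC 0.002, m = 280: SE = 0.0197, chance about 28%.
- ICC 0.01, m = 350: SE = 0.0299, chance about 61%.
- ICC 0.01, m = 280: SE = 0.0307, chance about 63%.

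The one-sided test in Section 3.7 would hold this error at 5%.

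**The case against.** **The analysis is not tied to a zero-difference null.** Section 3.9 names no null hypothesis, link or effect measure. A reader might infer that the planned analysis cannot support a non-inferiority claim at all. The text does not support that. The same GEE would serve once its confidence limit for the risk difference is read against -0.05. What is missing is the decision rule and a single alpha, not a new design.

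**Nobody says P >= 0.05 will be read as similar.** This is correct. Section 1.3 is background and Section 2.0 speaks of estimation. The figures in Step 4 are conditional on that reading and do not predict what the investigators will do.

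**The SAP may settle it.** The form of the interval and the link are usual SAP content. But Section 3.9 covers all P values without exception, so a SAP that applied the one-sided test of Section 3.7 would contradict it. The conflict lies in the protocol text itself.

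**A significant deficit could coexist with non-inferiority.** This is true in general, but for a worse monthly result it needs SE below 0.05/(1.96 + 1.645) = 0.0139. The planned SE is 0.0176.

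**Intention-to-treat only.** Section 3.9 says "All analyses will use the intention-to-treat principle and account for the stratified cluster design", and a reader might infer that a non-inferiority trial must add a per-protocol set. This is not an error in the plan, and an added set is commonly left to the SAP. Caregivers in both arms are told to return between visits if a sign of concern develops (Sections 3.5 and 4.6), so such returns are part of the plan and not contamination. A set defined by attending as scheduled would also select children differently by arm: weekly visits up to week 12 against four scheduled visits, and default after three missed visits against one (Section 4.8).

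**Conclusion.** The conflict is real and in the current text. Section 3.7 fixes a margin of -0.05 and one-sided 0.05. Section 3.9 fixes 2-sided 0.05 throughout and gives no margin rule. The stated 88% belongs to the first. At the second, power is about 81% with 350 analysed per site.

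The figure of about 75% holds only if the 20% loss comes out of the 350. Section 3.7 leaves this open by giving "a sample size of 350 children per health facility (2100 per group": 2100 equals 5 x 350 x 1.2, which suggests loss added on top of 350. That is a separate matter and is not settled here.

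The results rest on 5 sites per arm, a true difference of 0 for power, the protocol's ICC values, and normal quantiles, which reproduce the protocol's table. The finding concerns the decision rule and the alpha, not the GEE method or the intention-to-treat population.

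**What to change.** In Section 3.9, state that the primary analysis estimates the risk difference in recovery, monthly minus weekly, from the GEE with a confidence interval, and that non-inferiority is concluded if the lower limit is above -0.05. Then use one alpha in Sections 3.7 and 3.9:

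- a 2-sided 95% interval, with the power in Section 3.7 restated at ICC 0.002 as about 81% for 350 analysed per site or about 75% for 280; or
- one-sided 0.05 (a 90% interval), with the primary test exempted from the 2-sided rule and 88% kept for 350 analysed per site.

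The cost is a few sentences in two sections. The first option also lowers the stated power. No change to the design or data collection is needed.
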